## Abstract

**Background:**

Type 2 diabetes mellitus (DM2) is a disease with high prevalence and significant impact in terms of mortality and morbidity. The increased prevalence of the disease requires the implementation of new strategies to promote patient self-management. The Spanish Diabetes Self-Management Program (SDSMP) has proven to be effective in other settings. The objective of this study is to assess its effectiveness in terms of care for DM2 patients in primary care settings within the Basque Health Service – Osakidetza (Spain).

**Method/Design:**

This is a randomised clinical trial in which patients diagnosed with DM2, 18–79 years of age, from four health regions within the Basque Health Service will be randomised into two groups: an intervention group, who will follow the SDSMP, and a control group, who will receive usual care in accordance with the clinical guidelines for DM2 and existing regulations in our region. The intervention consists of 2,5 hour-group sessions once a week for six weeks. The sessions cover target setting and problem solving techniques, promotion of physical exercise, basic knowledge of nutrition, proper use of medication, effective communication with relatives and health professionals, and basic knowledge about DM2 and its complications. This content is complemented by educational material: books, leaflets and CDs. The primary outcome measure will be the change in glycated haemoglobin (HbA1c), and secondary outcome measures will include changes in levels of physical activity and intake of fruit and vegetables, cardiovascular risk, quality of life, self-efficacy, number of consultations and drug prescriptions. The results will be analysed 6, 12 and 24 months after the intervention.

**Discussion:**

If the intervention were to be effective, the programme should be spread to the entire diabetic population in the Basque Country and it could also be applied for other diseases.

**Trial registration:**

ClinicalTrials.gov identifier NCT01642394

## Background

Managing patients with chronic health problems represents a challenge for health services. According to the 2007 Basque Health Survey, chronic diseases are increasingly prevalent in our setting, currently, 83.5% of women and 86.1% of men aged over 65 years having some type of chronic condition [1]. In the health system, 80% of primary care consultations are related to chronic diseases, as 60% of hospital admissions and 70% of health expenditure [2].

In particular, the incidence of type 2 diabetes mellitus (DM2) has increased in our region in recent years. Indeed, it is predicted that prevalence of DM2 may reach up to 12% in the population over 30 years of age [3]. Mortality and morbidity in DM2 patients are known to be much higher than those in the general population; specifically, in diabetic patients, the mortality rate ranges from 13 to 30 deaths per 100,000 people per year, and 75% of these deaths are due to heart disease [3]. Further, it has been estimated that diabetes accounts for as much as 6.3 to 7.4% of health expenditure in our health system, while 42% of people with diabetes in our region are obese, 79.6% have high blood pressure and 22% have diabetic macroangiopathy [4]. According to the latest internal assessment data, there is room for improvement in diabetes control in our setting. Well-controlled diabetic patients, that is, those with HbA1c levels below 7%, represent just 44% of the overall diabetic population, and blood pressure is under 140/90 in only 25% of patients (unpublished data from internal assessments in the Basque Health Service, Osakidetza).

Health systems need to provide more efficient and coordinated care to patients with chronic conditions and this should be focused on decreasing rates of deterioration and improving the quality of life of patients and their families/caregivers. In relation to this, primary care has an essential role [2]. As in other developed countries, the Spanish Health System is outdated, and a new organisational model is needed to respond to the challenge of providing care to chronic patients [5]. Though several models have been proposed, the Chronic Care Model and the Kaiser Permanente model are among the most used and studied [2].

In both models, a key role is given to self-management and educational programmes, implying patient involvement in the management of their own condition. Among such programmes, the most widely used and studied structured approach is that of the Chronic Disease Self-Management Program (CDSMP) developed at Stanford University. The CDSMP is based on the self-efficacy theory of Albert Bandura [6], a social cognitive theory, which establishes two key factors in the achievement of successful behavioural change: confidence (self-efficacy) in one’s ability to perform a task, and the expectation of achieving a specific target (outcome expectation).

Despite the many systematic reviews published on the efficacy of different self-management education models [7-9], observed outcomes are heterogeneous due to the variable duration of study periods, types of interventions and target populations. What is more, programmes have not been assessed over the long-term.

In our setting, the pilot studies using this method have been promising, but have not yet been rigorously and prospectively evaluated compared to usual care [10]. A very recent trial, conducted in a different healthcare context, in male war veterans in the United States, has demonstrated that an educational intervention led by patients themselves is more effective for controlling glycaemic levels than one run by nurses [11]. Another recent study of a patient-led intervention, in primary care in Ireland, peer support found that the intervention was not effective in decreasing HbA1c levels in DM2 patients; however, the programme used was designed by the research team and placed more emphasis on social support than educational aspects [12], which is a different approach to that of the Spanish Diabetes Self-Management Program (SDSMP).

The Health Department of the Basque Country Government is promoting a new strategy for chronic patient care based on the Chronic Care Model (http://cronicidad.euskadi.net). Two of the cornerstones of this model are self-care promotion and population education. In this context, the “Active Patient” programme, based on the SDSMP which shares core elements with the CDSMP, has been proposed as a useful instrument for promoting self-care in patients with DM2. In order to assess the effectiveness of this programme, compared to usual care for DM2 patients in the Basque Health Service, we decided to conduct a clinical trial. The present paper describes the protocol we have designed for that purpose.

## Methods/design

### Primary objectives

To assess the effect of the SDSMP on glycaemic control in DM2 patients compared to usual care provided to this type of patient in primary care in the Basque Health System.

### Secondary objectives

● To assess any changes in

 o level of cardiovascular risk

 o quality of life

 o self-efficacy

 o physical activity

 o eating habits

● To evaluate the use of health resources by diabetic patients

● To assess the impact of the SDSMP on drug prescription and associated costs

● To describe the feasibility of implementing SDSMP within primary care in the Basque Health System.

### Hypothesis

An educational intervention for DM2 patients, based on the SDSMP, will be conducted by two leaders. At least one of them will be a chronic patient and have previously received specific training. This intervention will improve metabolic control, with a decrease of 0.5% or more in HbA1c levels [13], in comparison to usual health education.

### Design

A randomised clinical trial will be carried out in four health regions of the Basque Health Service (Araba, Gipuzkoa, Ezkerraldea-Enkarterri and the Bidasoa Integrated Health Organisation) involving a total of 556 DM2 patients between 18 and 79 years old, recruited proactively, as described in the section on the recruitment process below. Patients will be randomly assigned to intervention and control groups, and will be followed up over two years. Measurements will be taken at four time points: baseline, and 6, 12 and 24 months after the intervention. The research protocol has been approved by the Basque Country Clinical Research Ethics Committee (Ref. no.: 11/2010).

### Study subjects

#### Eligibility criteria

Patients must be 18 years old or above and have DM2, must be from one of four aforementioned health regions within the Basque Country, and must agree to participate in the Active Patient programme: “*Paciente Activo-Paziente Bizia*”.

#### Exclusion criteria

We will exclude individuals over 80 years of age, those with mental disorders associated with a loss of a sense of reality (schizophrenia, bipolar disorder, Alzheimer´s disease, psychosis or dementia) and those with any associated morbidity that might impede their participation in the course, such as is the case for chronic patients requiring home care.

#### Recruitment process

Eligible patients will be recruited in several ways: through advertisements for volunteers in the local media; by sending letters addressed to patients diagnosed with DM2, based on data from the Osabide electronic health record; and by their assigned health professionals (general practitioners and nurses) directly inviting them to participate.

Patients will be informed about the objectives of the study, and those willing to participate will be randomly assigned to intervention or control groups, after giving written informed consent. The baseline measurements will be taken before the randomisation process (Figure 1).

**Figure 1 F1:**
[figure not shown]
Flowdiagram for the study.

#### Withdrawal from the study

Participants will be able to withdraw from the study at any point if they wish. Those in the intervention group must participate in a minimum of four educational sessions; else, they will be considered as dropouts. All those randomised will, nevertheless, be included for the statistical analysis (i.e., data will be analysed on an intention-to-treat basis).

### Randomisation

Randomisation will be performed centrally by staff other than those of the research team, using a computer-generated random number sequence and after taking the baseline measurements.

### Standardization of the intervention

#### Intervention group

The complete intervention consists of group sessions (8 to 15 people) lasting 2.5 hours, once a week for six weeks. These sessions are structured with the aim of enabling participants to acquire knowledge and skills related to the disease and its management, placing a strong emphasis on proactive tools to achieve healthier lifestyles (in terms of diet, physical exercise, management of emotions, and correct use of medication, among others).

During the sessions, patients will be taught how to set realistic achievable targets, cope with problems related to their disease, communicate more effectively with relatives and health professionals sharing their feelings, and, overall, have an active attitude towards managing their disease and towards more healthy lifestyles. The sessions are supported by educational materials: books, leaflets and CDs.

Each group will be supervised by two leaders, who have previously been trained in the SDSMP. This training consists of two parts: the first, 24-hours of theoretical training, given by two Master Trainers certified by Stanford University; and, the second, practice, which involves trainees running a workshop with patients. Having completed these two components of the training, they can be certified as leaders. At least one of the two leaders should be a chronic patient him/herself or caregiver for a chronic patient. Leaders who are themselves chronic patients, or have close personal experience of a chronic condition, show greater empathy and tend to suggest more appropriate and realistic options than health professionals. The other leader, who is a doctor or nurse, should introduce himself to patients on the courses as an SDSMP programme leader, rather than as a health professional, as this strengthens the idea of peer education.

#### Control group

Patients assigned to the control group will receive usual care for secondary prevention of DM2 in accordance with the Osakidetza primary care protocols, which are based on clinical practice guidelines [14].

### Outcome variables

Baseline measurements will be taken prior to randomisation. As noted above, the clinical data will be collected at each health centre by collaborating health professionals, previously trained by the research team. Some instruments to be used are for self-completion by patients, while others are questionnaires for use by interviewers previously trained by the research team.

Blood samples will be collected by staff at the patients’ assigned health centres, and the analysis will be performed at the reference laboratories of the four participating health regions.

#### Primary outcome measure

Change in glycosylated haemoglobin (HbA1C) levels

#### Secondary outcome measures

Changes in the following:

● Body weight, height and BMI measured in standard conditions

● Systolic and diastolic blood pressure (SBP and DBP) measured by a validated automated sphygmomanometer following the recommendations in the 2007 Osakidetza clinical practice guidelines [14]

● Total and HDL cholesterol levels

● REGICOR cardiovascular risk scores [15]

● Quality of life assessed by the Spanish version of the ADDQoL-19 [16]

● Self-efficacy assessed using the Diabetes Self-efficacy Scale from Stanford University, and the level of physical activity assessed by the 7-day Physical Activity Recall (PAR) [17] questionnaire

● Mediterranean-Dietary Quality Index (PREDIMED Study)

● Medication taken for DM and associated risk factors (hypoglycaemic, antiplatelet, antihypertensive and lipid-lowering medication)

● Daily expenditure on medication

● Use of health services (number of visits to the doctor or nurse, admissions due to diabetes-related metabolic decompensation)

#### Independent variables

Age; sex; number of years since diagnosis of diabetes; history of diabetic microvascular disease: retinopathy, nephropathy or neuropathy; history of diabetic macrovascular disease: heart disease, peripheral arterial disease or cerebrovascular accident; treatment with anti-hyperglycaemic drugs: oral hypoglycaemic agents or insulin; and preventive cardiovascular medication: antiplatelet, antihypertensive and lipid-lowering drugs.

#### Variables related to the group intervention

Leader conducting the sessions

#### Variables related to the implementation

Percentage of the overall diabetic population invited who agree to participate in the programme; percentage of patients who agree to participate that then complete the programme; number of patients who go on to become trainers for the “Active Patient” programme; results of the satisfaction survey; number and percentage of health professionals involved at each centre who conduct the regular check-ups for diabetes patients participating in the research; and number and percentage of professionals who become trainers in the Active Patient programme.

Both the intervention and control groups will have four sets of measurements taken: prior to the intervention and 6, 12 and 24 months after the intervention.

### Data management

The research team will run a training session for collaborators in the health centres, to ensure consistency in the data collection. In addition, printed and electronic support material will be available in each participating centre.

The researchers at each centre will collect the data using a form designed for this purpose. These data will be then stored in a password-protected Access database using double-data entry designed for the purpose. Similarly, the interviewers will enter the data into an Access database designed for the purpose. A report on the quality of data obtained will be produced once a month.

### Sample size

Based on the results of a pilot study with 171 patients, we found a standard deviation (SD) of 1.2% in HbA1c and, given that that the mean SD in literature is around 2%, we used an SD of 1.5% to calculate the sample size. Considering an intra-class correlation of 0.05 [18] and an average of 10 participants per group, we calculated that we needed 277 participants per study arm to detect a clinically relevant difference of 0.5% in HbA1c levels at 12 months, with 80% power, with p-value of 0.05 and assuming a dropout rate of 15%.

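### The stated sample-size inputs give about 241 to 244 patients per arm, not 277, so the size or one of the inputs is misreported, in the conservative direction

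*Protocol article*

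**What the plan says.** The Sample size section of the protocol article gives both the inputs and the result.

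- SD: the pilot gave 1.2% and the literature value is about 2%; between these, "we used an SD of 1.5% to calculate the sample size".
- Clustering: "Considering an intra-class correlation of 0.05 [18] and an average of 10 participants per group".
- Target: "to detect a clinically relevant difference of 0.5% in HbA1c levels at 12 months".
- Error rates and loss: "with 80% power, with p-value of 0.05 and assuming a dropout rate of 15" per cent.
- Result: "we calculated that we needed 277 participants per study arm to detect a clinically relevant difference of 0.5% in HbA1c levels at 12 months". No formula or intermediate figure is shown.

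The Design section describes a trial "involving a total of 556 DM2 patients between 18 and 79 years old".

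**The concern.** The paragraph states everything needed to recompute the size, and the recomputation does not give 277. The calculation concerns HbA1c, the primary outcome, so it is the justification for the size of the whole trial. If the result and the inputs disagree, a reader cannot tell which assumption was really used, what power the trial has, or how many patients are to be recruited. The two sections also disagree on the total: 2 × 277 = 554, not 556.

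**Working it through.** **Inputs.** All are from the Sample size section: SD 1.5%, difference 0.5%, intra-class correlation 0.05, average group size 10, power 80%, significance level 0.05, dropout 15%. Two assumptions are added: a two-sided test (sidedness is not stated) and 1:1 allocation (one figure is given for each arm).

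**Attempt to reproduce 277**

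1. Individually randomised size per arm: 2 × (1.960 + 0.8416)² × 1.5² / 0.5² = 141.3, or 142 rounded up.
2. Design effect: 1 + (10 − 1) × 0.05 = 1.45.
3. After clustering: 141.3 × 1.45 = 204.9.
4. After dropout: 204.9 / 0.85 = **241.0** per arm.

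Rounding to 142 at step 1 gives 205.9 / 0.85 = 242.2. Starting from the t-test size (142.2, or 143 rounded up) gives 242.7 to 243.9. The range is therefore about 241 to 244 per arm, and the stated 277 is 33 to 36 per arm higher. Against 241 the excess is 15%, or 72 patients in total.

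**Variants that keep the stated inputs and apply dropout once**

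| Variant | Per arm |
|---|---|
| Dropout as × 1.15 instead of / 0.85 | 236 to 239 |
| One-sided 0.05 | about 191 |
| Design effect taken as 1 + 10 × 0.05 = 1.50 | 251 |
| Group size after dropout, 8.5 | 230 |
| Design effect in the intervention arm only | 204 |

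None comes close to 277.

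**Changes to an input or step that land near 277**

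| Change | Calculation | Per arm |
|---|---|---|
| Power 85% | 162 × 1.45 / 0.85 | 276.4 (275.7 without rounding to 162) |
| Group size 14 | 142 × 1.65 / 0.85 | 275.6 (277.6 from 143) |
| Group size 15, dropout as × 1.15 | 142 × 1.70 × 1.15 | 277.6 |
| SD 1.6% | 161 × 1.45 / 0.85 | 274.6 |
| Dropout twice, mixed forms | 204.9 / 0.85 × 1.15 | 277.2 |
| Dropout twice, same form | 204.9 / 0.85², or 204.9 × 1.15² | 283.5 or 270.9 |

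Several different changes reach 277 or nearly so, and the arithmetic cannot choose between them.

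**Power at the stated size**

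- Retained: 277 × 0.85 = 235.5 per arm. Effective: 235.5 / 1.45 = 162.4.
- Standard error: 1.5 × √(2 / 162.4) = 0.166.
- Power: Φ(0.5 / 0.1665 − 1.960) = Φ(1.04) = **85.2%** (85.0% by the t-test).
- Difference detectable at 80% power: 2.8016 × 0.1665 = **0.47%**.
- With 278 per arm (556 / 2) the power is 85.3%, so the choice between 554 and 556 has no statistical weight.

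**The case against.** The best defence is that the discrepancy is on the safe side. The promised 80% power is met and exceeded under the stated inputs, no bias follows, and two patients' difference in the total is editorial. The extra patients also have some value: the SD of 1.5% is a compromise with a literature value near 2%, and at 277 per arm the power is still about 80% if the SD is 1.6%, but about 61% if it is 2.0%. All of this stands, and it argues against cutting recruitment to 241. It does not rescue the paragraph. Nor does the shortness of a journal article, because the inputs and the result are both printed and they disagree.

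Three stronger readings are tempting, and the article does not support them.

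- *Dropout was counted twice.* The match at 277.2 needs two different forms in sequence (/ 0.85, then × 1.15); the same form used twice gives 271 or 284. A single allowance with 85% power, or with groups of 14 to 15, does as well. Double counting is one possibility only.
- *The trial is underpowered.* The reverse holds under the stated inputs: 80% understates the power.
- *The design effect was wrongly applied to the control arm.* It is true that "Patients assigned to the control group will receive usual care", but the article does not say to which arms the design effect was applied. Inflating both would be conservative, and inflating one gives 204, further from 277.

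**Conclusion.** The point holds as an internal inconsistency. The stated inputs give about 241 to 244 per arm, and 277 per arm corresponds to about 85% power or a detectable difference of about 0.47% at 80% power. Either the size or one of power, group size, SD and dropout handling is misreported; the article does not allow anyone to say which.

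The conclusion rests on a two-sided test and equal allocation. A one-sided test widens the gap. The power figure also takes the stated SD, intra-class correlation, group size and 15% dropout as given.

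The consequence is limited. The justification of the trial's size cannot be reproduced and should be corrected, but the primary comparison is not weakened under the plan's own assumptions.

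**What to change.** Keep the recruitment target and correct the text.

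- Show the calculation step by step: size before clustering, design effect, then dropout applied once as n/(1 − 0.15). State that the test is two-sided, if it is.
- If the printed inputs are the ones intended, restate the power at 277 per arm as about 85%. If another input was used, print the input that actually yields 277. Alternatively, state that 80% power needs about 241 to 242 per arm and that the target exceeds this.
- Use one total throughout: 277 per arm is 554, and 556 is 278 per arm.

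The cost is the wording of one paragraph and one total. No additional patients, visits or analyses are needed.

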### Data analysis

The categorical variables will be presented as frequencies and percentages (%) while the continuous variables will be reported as means and SDs. Patients in the intervention and control groups will be compared on an intention-to-treat basis. To assess the intervention effect, we will compare changes observed in each of the groups using Chi-square tests for categorical variables, and Student’s t-tests for continuous variables in the two independent groups, for each of the repeated measurements. To adjust variables that may confound or moderate the effect of the intervention, we will perform stratified analysis and multivariate regression analysis. Multilevel analysis, i.e., generalized mixed-effects models, will be used to estimate baseline and multivariate-adjusted between-group mean differences, adjusted odds ratios (AORs), and 95% confidence intervals (CIs) at the patient level, taking into account the clustered structure of data for patients for whom the intervention has been led by different individuals.

Longitudinal generalized mixed models will be used to analyse the overall trend in changes in the outcome measures taking into account the repeated measurements for each patient and also the clustered structure of data. These models will be linear for continuous variables, and logistic for categorical variables. Time will be considered in these models as a continuous variable, based on linear, quadratic or logarithmic functions, or as a categorical variable, with several correlated measurements for each individual. The least restrictive option with the best fit to the data will be chosen. The intervention, the time of measurement and intervention-time interaction will be included as fixed effects in the models. Patients and leaders will be included as random effects on the intercept and on the time slope. These models will be extended to include variables that may confound or modify the effect of the intervention, this being guided by the stratified analysis. At this stage, results will be presented as coefficients with their respective 95% confidence intervals. The analysis will be performed using SAS v. 9.2, SPSS v. 19 and R.

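### The stated test of effect is an unadjusted t-test on change scores, and no model clearly names baseline HbA1c as a covariate, so precision is given away

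*Protocol article*

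**What the plan says.** The primary outcome is "Change in glycosylated haemoglobin (HbA1C) levels" (Primary outcome measure). Baseline is measured before randomisation (Recruitment process, Randomisation, Outcome variables), so each randomised patient should have a baseline value.

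The Data analysis section then describes three layers of analysis:

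- For the intervention effect, "we will compare changes observed in each of the groups", with "Student’s t-tests for continuous variables in the two independent groups, for each of the repeated measurements". No adjustment is attached to this test.
- Stratified and multivariate regression, and multilevel models that "will be used to estimate baseline and multivariate-adjusted between-group mean differences".
- Longitudinal mixed models: "The intervention, the time of measurement and intervention-time interaction will be included as fixed effects in the models". Time may be continuous or categorical, and further covariates are added under the guidance of the stratified analysis.

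The list under Independent variables, which opens "Age; sex; number of years since diagnosis of diabetes", goes on to complications and medication. It does not include HbA1c at baseline. No analysis is designated as primary. In the Sample size section, "we used an SD of 1.5% to calculate the sample size"; this is described as an SD of HbA1c, not of its change.

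**The concern.** Baseline HbA1c is likely to be the strongest predictor of 12-month HbA1c, and it is already measured. A change score uses it inefficiently, because it subtracts the whole baseline value when only a fraction r of a baseline deviation is expected to persist. Two things follow. The estimate is noisier than it need be. And if the arms differ at baseline by chance, the change score over-corrects, subtracting (1 − r) times that difference too much.

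The later models do not clearly repair this. The phrase about baseline and multivariate adjustment can mean differences adjusted for baseline, or differences at baseline followed by adjusted differences. In the longitudinal model, if time is categorical and the intervention term is free at baseline, the intervention-by-time contrast is again essentially a difference of changes. With no analysis named as primary, a reader cannot tell whether the efficient analysis would carry the conclusion.

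**Working it through.** **Inputs.** From the Sample size section: difference 0.5, SD 1.5, intra-class correlation 0.05, 10 per group, 80% power, significance level 0.05 (taken as two-sided), 15% dropout, 277 per arm. Assumed: the correlation r, equal SDs at baseline and follow-up, and the same design effect for every analysis.

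**The plan's own figure.** Independent patients: 2 × (1.5 × (1.960 + 0.842) / 0.5)² = 141.3 per arm. Design effect: 1 + 9 × 0.05 = 1.45, giving 204.9. Dividing by 0.85 gives 241.0, or 242 if each step is rounded up. The stated 277 does not reproduce from these inputs; it is larger than they require. With 277 per arm and 15% dropout, 277 × 0.85 = 235.45 are evaluable, or 162.4 effective patients per arm, and power at SD 1.5 is 85%. That margin counts in the plan's favour below.

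**Residual SD by analysis.**

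- Change score: 1.5 × √(2(1 − r)). This equals 1.5 only at r = 0.5.
- Baseline-adjusted (ANCOVA): 1.5 × √(1 − r²).
- Variance ratio, change to ANCOVA: 2(1 − r)/(1 − r²) = 2/(1 + r), which is never below 1.

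**Power at 277 per arm.** The standard error is SD × √(2 × 1.45/235.45) with clustering in both arms, or SD × √((1 + 1.45)/235.45) with clustering in the intervention arm only. Each power cell shows both arms / intervention arm only.

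| r (assumed) | Variance ratio | Change-score power | ANCOVA power |
|---|---|---|---|
| 0.3 | 1.54 | 0.719 / 0.789 | 0.883 / 0.929 |
| 0.5 | 1.33 | 0.852 / 0.905 | 0.934 / 0.965 |
| 0.7 | 1.18 | 0.972 / 0.988 | 0.988 / 0.996 |

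**Where the t-test drops below 80%.** The standard error must not exceed 0.5/2.802 = 0.178.

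- Clustering in both arms: 0.178/0.1110 gives a largest tolerable change SD of 1.61. Then 2(1 − r) = 1.61²/2.25 = 1.15, so r is about 0.43.
- Clustering in the intervention arm only: 0.178/0.1020 gives 1.75. Then 2(1 − r) = 1.36, so r is about 0.32.

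**Patients needed per arm** (design effect 1.45 in both arms, 15% dropout), change score against ANCOVA: 338 against 220 at r = 0.3; 242 against 182 at r = 0.5; 145 against 124 at r = 0.7.

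**Chance imbalance.** With independent patients and 277 per arm, the standard error of the baseline difference is 1.5 × √(2/277) = 0.127. A difference of 1.96 standard errors is therefore 0.25% HbA1c. The change-score contrast is shifted by (1 − r) × 0.25: about 0.12 at r = 0.5 and 0.07 at r = 0.7, against a target of 0.5.

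**The case against.** The strongest reply is that the article does plan adjusted analyses, and that the list of independent variables is not said to be the complete adjustment set. HbA1c appears there as the outcome, so its absence from a list of other characteristics does not show that it is excluded from the models. An exact covariate list may also sit in a fuller document. This stands. A reader might infer that baseline imbalance goes uncorrected throughout, but the text does not support that: the adjusted models may well include baseline, and a change score over-corrects imbalance rather than ignoring it.

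A reader might also call the t-test the primary analysis. The article names none, and paragraph order is not a hierarchy. Nor does the longitudinal model always reduce to a difference of changes. If time is modelled as a linear, quadratic or logarithmic function, the contrast is a difference of trajectories over four measurements.

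On power, the shortfall needs a low correlation. Controls receive usual care, and the clustering described is by who led the intervention, so the intervention-arm-only case fits the design better. There, r = 0.3 gives 79%, one point short.

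Finally, one might want region in the model because "the analysis will be performed at the reference laboratories of the four participating health regions". But a constant laboratory offset cancels within a patient's change, and the article reports no assay difference.

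None of this answers the core point. The test stated for the intervention effect is unadjusted, and where adjustment is mentioned its wording does not settle the role of baseline HbA1c.

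**Conclusion.** The point holds as one of efficiency and clarity, not validity. The t-test on changes is unbiased over randomisation. Relative to baseline adjustment, its variance is 18% to 54% larger for r between 0.7 and 0.3. Planned power is at risk only if r is below about 0.43 (clustering in both arms) or 0.32 (intervention arm only). At r = 0.5 it is 85% to 90%, and it rises with r. A 1.96-standard-error chance imbalance at baseline would move the change-score estimate by about a quarter of the 0.5 target at r = 0.5.

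All of these sizes depend on r, which the article does not give. The direction does not: in large samples, baseline adjustment is at least as precise at any r. It would be wrong to conclude that the trial is underpowered or that baseline is ignored.

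**What to change.** Name one main analysis of HbA1c at 12 months: a model of follow-up HbA1c with treatment arm and baseline HbA1c as fixed, pre-specified covariates, keeping the planned leader-level clustering. An equivalent route is the longitudinal mixed model with time as categorical and baseline means constrained equal across arms. Replace the ambiguous phrase on baseline and multivariate adjustment with a statement of which baseline value enters which model. Treat each continuous secondary outcome in the same way, using its own baseline. The t-tests on changes can stay as a descriptive supplement. A fixed effect for health region is optional.

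The cost is analysis wording only. Baseline is already measured before randomisation, so no data, visits or patients are added.
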